Further, during visit 1, the cardiac nurse will also record the diagnostic reason for referral (MI: location, severity, number of stents, ejection fraction), medication prescribed and level of risk for cardiac rehabilitation. At visit 4, the cardiac nurse will assess whether the patient can return to work. Patients will be administered a satisfaction survey with questions selected from the local public health department’s satisfaction questionnaire.

Blood tests will be performed at visits 1, 2 and 4. The following parameters will be determined: hemoglobin, leucocytes, platelets, urea, creatinine, sodium, potassium, cholesterol, high density lipoprotein cholesterol, low density lipoprotein cholesterol, triglycerides, creatine kinase-MB (CK-MB), C-reactive protein, glycosylated hemoglobin A1c (HbA1c), N-terminal Pro-B-type natriuretic peptide (NTproBNP), microalbumin and calcidiol.

The patient will do the exercise stress test at visit 1 and 2, under the guidance of the cardiologist and the nurse. The Bruce protocol stress test will be used. Before starting, the staff will describe the test to the patient and give some recommendations such as taking a light meal three hours before the test, avoiding stimulating drinks, taking prescribed medication and wearing comfortable shoes and clothes. In this protocol, exercise is performed on a treadmill (QUINTON® Q-STRESS TM 55). The leads of the ECG are placed on the chest wall. The treadmill is started at 2.74 km/hr (1.7 mph) and at a gradient (or incline) of 10%. At three minute intervals the incline of the treadmill increases by 2%, and the speed increases progressively. The exercise stress test will be limited by clinical signs such as arrhythmias and/or ECG changes and clinical symptoms such as general exhaustion, claudication of the legs, chest pain or dyspnea [13].

The following exercise stress variables will be recorded: theoretical maximum heart rate, real maximum heart rate, baseline heart rate, chronotropic index, the level reached on the exercise stress test, and time to recover initial heart rate (1 and 3 minutes). The cardiac nurse will collect blood before and after the exercise stress test in order to determine the level of troponin I.

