### Demographic and clinical measures

Group allocation, sex, age, education level, marital status, living situation, employment status, main diagnosis, diagnostic reason for referral, location, degree of involvement, number of stents, the ejection fraction, comorbidities (Charlson Comorbidity Index), maximum theoretical heart rate, real maximum heart rate, baseline heart rate, chronotropic index, the level reached on the exercise stress test, time to recover initial heart rate (1 and 3 minutes)), level of risk for cardiac rehabilitation, blood tests, cardiac markers (NTproBNP, troponin I), SBP, DBP, BMI, abdominal circumference, Mediterranean diet, depressive symptoms (Yesavage Depression Scale), basic activities of daily living (Barthel Index), tobacco consumption (Fargeström test), compliance with cardiac medication (Haynes-Sackett method), taking sublingual nitroglycerin, physical activity (Caspersen and Powell classification) and return to work.

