### Statistical issues

#### Sample size

To ensure a statistical power of 80% in order to detect differences in the contrast of the null hypothesis (H_0_: equal percentages of cardiac readmissions in the two groups) through a two-tailed chi-square test for two independent samples, with a level of significance of 0.05, and assuming that the percentage of cardiac readmissions in the control group is 25% and the percentage in the intervention group is 12%, each group will require 139 patients. Assuming a 5% loss to follow-up, we estimate that 146 patients will be needed in each arm.

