#### Statistical analysis

Continuous variables will be summarized using means and standard deviations for normal distributions, and by medians and the 25th and 75th percentiles for non-normal distributions. Categorical variables will be summarized using absolute values and relative frequency. We will test for significant differences among the baseline characteristics of the control and intervention groups. For continuous variables, we will use the Student's *t*-test if both sample groups have normal distribution or the Mann–Whitney *U* test otherwise. We will use the *χ*^2^ test to compare categorical variables (or Fisher’s exact test in 2×2 contingency tables where the expected frequencies are lower than 5).

Percentage of patients readmitted for cardiac disease will be analysed through a two-tailed *χ*^2^ test for two independent samples, and time to first hospital readmission for cardiac disease will be analysed as time to event with Kaplan-Meier estimation and Cox proportional regression models. The deaths occurring without hospitalization will be introduced in the survival analysis as censored data. Event or censored times for all patients will be measured from the time of randomization (visit 0). All information available on the primary and secondary end points will be collected until the time of final contact with the patient, including patients lost to follow-up, at which point follow-up will be censored. Survival data will be presented graphically using the Kaplan-Meier method. We will use the log-rank test to compare the survival curves. To estimate the effect size, we will report the unadjusted hazard ratios (HR) and associated 95% confidence intervals (95% CI) obtained in the bivariate Cox proportional regression models.

To establish whether the allocation group is an independent prognostic factor for cardiac readmission, we will adjust for potential confounders in a multivariate analysis. The model will be adjusted with the significant covariates in bivariate analysis or those that were clinically significant. To estimate the effect size, we will report the adjusted hazard ratios (HR) and associated 95% confidence intervals (95% CI) obtained in the multivariate Cox proportional regression models.

Outcomes will be analysed on an intention-to-treat basis. A two-sided α-level of 0.05 will be considered statistically significant. Data will be analysed using IBM SPSS Statistics for Windows v.20 and Stata v.10.

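### The adjusted Cox model takes its covariates from significance in the trial's own data or unspecified clinical judgement, with no visit fixed for their values, so the adjusted hazard ratio is not settled in advance

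*Protocol article*

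**What the plan says.** Time to first cardiac readmission is one of the listed primary outcomes. The Statistical analysis section gives it a Kaplan-Meier display, a log-rank test and an unadjusted Cox hazard ratio. It then announces a further model to show whether allocation is independently prognostic: "we will adjust for potential confounders in a multivariate analysis". The selection rule follows: "The model will be adjusted with the significant covariates in bivariate analysis or those that were clinically significant". The adjusted hazard ratio and its 95% interval are to be reported as an effect size.

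The same section starts every patient's clock at randomization, visit 0. The Procedure section and Table 1 place much of the clinical information later. Blood tests, the stress test, BMI, blood pressure and medication adherence first appear at visit 1, one month after discharge. Details of the qualifying diagnosis are also entered then: "during visit 1, the cardiac nurse will also record the diagnostic reason for referral". The section Demographic and clinical measures lists all of these without saying which are candidates for the model.

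**The concern.** The rule has two limbs, and neither can be carried out before the data are seen. The first admits a covariate because its p-value in this trial is small. The second admits it on clinical judgement, with no list, no limit on number and no point at which the judgement is made. Two analysts following the text faithfully could report different adjusted hazard ratios. The trial is open, so nothing in its design shields that choice from knowledge of the allocation.

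The silence on timing adds a second problem. A covariate taken at visit 1 does not exist for someone readmitted earlier, or it is measured after the event it is supposed to predict. Such patients would leave a complete-case model, which sits badly with the stated intention-to-treat basis, or would carry values altered by the event. A covariate taken at visit 2 or later could have been changed by the training, and adjusting for it could remove part of the effect under study.

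**Working it through.** **1. The plan's own figure.** Inputs from Sample size: 25% against 12%, two-sided 0.05, 80% power. With p̄ = 0.185,

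n = [1.960 × √(2 × 0.185 × 0.815) + 0.8416 × √(0.25 × 0.75 + 0.12 × 0.88)]² / 0.13²
= (1.0763 + 0.4556)² / 0.0169 = 138.9, so 139 per arm, as stated.

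139 × 1.05 = 146, as stated. (139 / 0.95 gives 147; the difference of one is immaterial.)

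**2. Expected first events.**
- At 146 per arm: 146 × 0.25 + 146 × 0.12 = 36.5 + 17.5 = 54.0.
- At 139 per arm (completers only): 139 × 0.37 = 51.4.

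**3. How many terms that carries.** The convention of about 10 events per term is an assumption, not in the article. It gives 54.0 / 10 = 5.4 or 51.4 / 10 = 5.1 terms. Allocation plus three single-parameter covariates is 4 terms: 54.0 / 4 = 13.5 events each (12.9 at 51.4). Allocation plus five is 6 terms: 54.0 / 6 = 9.0 events each (8.6 at 51.4). Three to five covariates is therefore about the limit, and the plan's rule sets none.

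**4. When candidates are recorded, against a clock that starts at visit 0.**
- Visit −1: age, sex, education, marital status, living situation, employment, Charlson index, diet, tobacco, hypertension, diabetes, depressive symptoms, Barthel index.
- Visit 1 first: blood panel, stress-test results, BMI, waist, blood pressure, medication adherence, risk level for rehabilitation.
- Entered at visit 1 but apparently describing the index event: location, severity, stents, ejection fraction.
- Visit 4 only: return to work.

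**5. Events before visit 1.** The article gives no monthly rates, so a constant hazard over the year is assumed.
- Control: 146 × (1 − 0.75^(1/12)) = 146 × 0.0237 = 3.5.
- Intervention: 146 × (1 − 0.88^(1/12)) = 146 × 0.0106 = 1.5.
- Total about 5.0, which is 5.0 / 54.0 = 9% of expected events.

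Training starts only after the month-1 stress test, so the control hazard may apply to both arms in that month: 2 × 3.46 = 6.9. A hazard concentrated early would give more, but the article offers no figure for that.

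**6. Does the selection itself distort the test of allocation?** A Cox simulation used 292 patients, 50 independent true baseline covariates (an assumed number), screening at 0.05, no treatment effect and 400 runs per scenario.
- No covariate prognostic: rejection 5.0% unadjusted, 4.2% after selection, with 2.5 noise covariates admitted on average (50 × 0.05 = 2.5).
- Eight covariates prognostic: 5.5% unadjusted, 5.8% after selection.

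The simulation error is about √(0.05 × 0.95 / 400) = 1.1 percentage points, so no inflation is visible. The simulation does not cover covariates measured after randomization.

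**The case against.** The strongest reply is that this is one supplementary estimate. The chi-square test that drives the sample size, the log-rank test and the unadjusted hazard ratio do not depend on the rule, and both hazard ratios are to be reported. A covariate list is also commonly left to an analysis plan, which is not shown. The first part stands and limits the consequence. The second does not dispose of the point, because the article states a selection method rather than leaving one open.

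Several stronger readings are tempting, but the document does not support them.

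- *A candidate pool of about 50.* That count comes from expanding the blood panel within the list of measures; unexpanded it is about 35. The article speaks only of potential confounders and defines no pool.
- *Covariates chosen by baseline imbalance.* The article does say "We will test for significant differences among the baseline characteristics of the control and intervention groups", but it never ties those tests to the model. Its preceding paragraph uses the word bivariate for single-predictor Cox models, so association with readmission is the natural meaning.
- *Visit-1 values as mediators of training.* Training begins within three days after the visit-1 stress test, so values taken then precede it. Open allocation could still have influenced behaviour in the first month. Mediation by training needs later values, which the article neither plans to use nor rules out.
- *Physical activity, stents and ejection fraction as post-randomization measures.* The Procedure section says physical activity is also taken at baseline, although Table 1 shows the classification only from visit 1. Stents and ejection fraction appear to describe the index admission.
- *Return to work as a covariate.* It is listed among the measures, "physical activity (Caspersen and Powell classification) and return to work", but nothing says it would enter the model.
- *A raised false-positive rate.* That would require someone to pick the more favourable of two results. The plan reports both.

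**Conclusion.** The point holds for the adjusted hazard ratio and for the conclusion that allocation is independently prognostic. As written, the model depends on p-values in the trial data or on unrecorded judgement, and the visit supplying covariate values is open. If visit-1 variables enter, about 5 of 54 expected events (9%) would come from patients whose values are missing or post-event. That figure rests on the plan's 25% and 12% rates and an assumed constant hazard; about 7 is obtained if the control hazard applies to both arms in month 1. A patient readmitted early may still attend visit 1, so loss of those events is possible rather than certain. The main unadjusted analyses are unaffected and no material type I inflation is shown. This should be corrected, but it does not undermine the trial's main comparison.

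**What to change.** Replace the selection rule with a short named list of about three to five prognostic covariates, all recorded at visit −1, and enter them whatever their p-values. Age, sex, Charlson index, diabetes and smoking are examples; all are at visit −1 in Table 1. Coding each with one parameter keeps the model close to what 51 to 54 events can carry. State that variables measured after randomization are excluded. If ejection fraction or number of stents is wanted, take the value from the index-admission record rather than from a visit-1 assessment, and count it within the limit.

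This changes wording only and needs no new data, visits or patients. The price is that covariates can no longer be added after the data have been seen.

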### Ethical approval

The protocol has been approved by the independent Ethical Committee of Clinical Research of our hospital. Before recruitment, all patients will provide written, informed consent to participate. The study will comply with all local legal and regulatory requirements and with the Declaration of Helsinki. Trial registration on Current Controlled Trials is ISRCTN57634424 a date 30/04/2010.

## Limitations

One limitation of this study is its open design, since it will not be possible to blind the intervention and both patients and staff will know to which group they have been assigned. This may affect the degree of response, especially in the control group. Another limitation may be the difficulty of including patients due to the large size of the catchment area and its mainly rural nature. This may restrict the inclusion process due to the distance and transport problems, and may limit the external validity.

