Despite the acknowledged benefits, however, CRPs are currently underused. According to the European Cardiac Rehabilitation Inventory Survey (2008)[7,8], of the 47.5% of the countries that answered the survey, 42.10% (including Belgium, Spain, and Italy) admitted ≤ 30% of eligible patients for phase II of CRP; 15.79% (Luxembourg, Sweden, UK) admitted >30-50% of eligible patients, and 15.79% (Germany, Iceland, Lithuania) admitted >50%. Data were unavailable for the remaining 26%.

Studies on post-MI survival, readmissions and physical rehabilitation date back to 1972 [9]. Most studies have found no significant differences in readmissions post-CRP but in 2005 one study concluded that global community CRP significantly reduced cardiac readmission rates [10]. In 2011, Heran et al. [11] published an updated systematic review of Jolliffe et al’s 2001 study, finding that exercise-based CRPs significantly reduced hospital admissions in the short term (<12 months), and in the same year Lawler [12] published the first meta-analysis showing a statistically significant reduction in MI recurrence with an exercise-based CRP post-MI (OR 0.53; 95% CI: 0.38 - 0.76). Moreover, the few studies of the issue do not focus on identifying the best exercise regimen for reducing readmissions, but on whether the intervention itself affects readmission rates. Only two of the studies presented statistically significant decreases in readmissions [10,12]. The value of readmission as an indicator of effectiveness of exercise lies in the fact that it is an indirect measure of clinical stability, so there is a clear need to study the relation between CRPs and readmission in MI patients.

The aim of this study is to evaluate the efficacy of a supervised exercise training program for reducing cardiac readmissions in patients with MI in the first year after hospital discharge. This study will also provide a detailed evaluation of the program’s effects on total mortality, functional capacity, quality of life and adherence to regular exercise. Our primary hypothesis is that a supervised exercise training program will significantly reduce the incidence of cardiac readmissions in patients with MI in the first year after hospital discharge. The secondary hypothesis is that patients in the intervention group will present significantly better functional capacity, better quality of life, and lower mortality rate.

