### Assessment of outcomes

#### Primary outcome measures

The primary outcome measures will be the percentage of patients readmitted, total number of readmissions and length of hospitalization for cardiac disease during the first year after hospital discharge and time to first hospital readmission for cardiac disease. The primary outcome will be assessed by an expert committee blind to the patient’s treatment group.

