#### Secondary outcome measures

Secondary outcomes are the following: percentage of patients readmitted, total number of readmissions and length of hospitalization for all causes during the first year after hospital discharge, all-cause death, all-cause hospital emergency visits, functional capacity (exercise stress test), quality of life (EuroQol5), adherence to CRP (attendance at follow-up visits), adherence to cardiac pharmacological treatment (Haynes-Sackett test), satisfaction with assistance received (questions selected from the local public health department’s questionnaire, Ambulatory Specialized Care 2008 [14]).

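### Staff-driven bias in the effort-dependent visit 2 stress test, which carries the functional-capacity hypothesis, is partly avoidable, but the plan states masked assessment only for the primary outcome

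*Protocol article*

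**What the plan says.** The protocol article's Background sets the secondary hypothesis that "patients in the intervention group will present significantly better functional capacity, better quality of life, and lower mortality rate". Secondary outcome measures names the exercise stress test as the measure of functional capacity.

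On the conduct of the test, Procedure states: "The patient will do the exercise stress test at visit 1 and 2, under the guidance of the cardiologist and the nurse". Besides arrhythmias and ECG changes, it can be limited by "clinical symptoms such as general exhaustion, claudication of the legs, chest pain or dyspnea". The recorded variables are theoretical and real maximum heart rate, baseline heart rate, chronotropic index, level reached and heart-rate recovery.

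On masking, Primary outcome measures states: "The primary outcome will be assessed by an expert committee blind to the patient’s treatment group". No comparable statement is made for any secondary outcome. Limitations says "it will not be possible to blind the intervention and both patients and staff will know to which group they have been assigned", adds that this may affect the degree of response, particularly among controls, and makes no exception for the people who run the stress test.

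**The concern.** A test that may end on exhaustion or dyspnea depends on how hard the patient tries, how much the staff urge the patient on, and when the supervisor judges that it is over. If the staff know the arm, the last two can differ between arms without anyone intending it. The likely direction is more encouragement for trained patients or earlier stopping for controls, and both favour the hypothesis. The difference enters when the test stops, so no later analysis can remove it.

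Limitations presents staff awareness as a consequence of an intervention that cannot be blinded. For staff who deliver the training, that is true. For the cardiologist at visit 2 it does not follow from anything the article says. At stake is how far a better result in the intervention arm can be credited to training. The primary readmission outcome is not affected.

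**Working it through.** **1. Which test carries the hypothesis.** Procedure and Table 1 place the stress test at visits 1 and 2 only (months 1 and 3). Intervention starts training within three days of the visit 1 test. Visit 2 is thus the only test after training has begun.

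**2. Who knows the arm and who needs it.**

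| Person | Learns the arm? | Task that needs it? |
|---|---|---|
| Patient | Yes (Limitations) | Unavoidable |
| Physiotherapist | Yes (Randomization, Procedure) | Yes: supervises training |
| Cardiac nurse | Yes, as one of the two who obtain the allocation and book visits (Procedure) | Yes, for scheduling and follow-up |
| Cardiologist at visit 2 | Only through the general word for staff in Limitations | None stated |
| Outcome committee | No (Primary outcome measures) | None |

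The visit 1 test shapes the training programme (Intervention). No such use is stated for the visit 2 test.

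**3. Which variables are exposed.** Level reached, real maximum heart rate and chronotropic index all depend on when the test stops. Theoretical maximum and baseline heart rate do not. Heart-rate recovery, and stops for arrhythmia or ECG changes, are less open to encouragement.

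**4. The plan's own number.** The plan gives no figure for functional capacity. The number per arm comes from Sample size: 25% against 12%, two-sided 0.05, power 80%. With mean proportion 0.185 and difference 0.13:

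n = [1.960·√(2·0.185·0.815) + 0.842·√(0.25·0.75 + 0.12·0.88)]² / 0.13² = (1.076 + 0.456)² / 0.0169 ≈ 138.9, that is 139.

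The stated 139 per arm reproduces, and this point does not change it.

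**5. How much bias would matter.** Assumptions: 139 tested per arm, a continuous measure, no true effect, and a systematic difference of b SDs in favour of the intervention. The standard error of the difference is √(2/139) = 0.120 SD. The probability of a significant result favouring the intervention is Φ(b/0.120 − 1.960).

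| b (SD) | b / 0.120 | Probability |
|---|---|---|
| 0 | 0 | 2.5% |
| 0.1 | 0.83 | 13% |
| 0.2 | 1.67 | 39% |
| 0.3 | 2.50 | 71% |
| 0.4 | 3.33 | 92% |

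These values show sensitivity to bias. They do not show that a bias of any given size will occur.

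**The case against.** Several parts of the case on the other side stand.

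- **The cardiologist's knowledge is inferred.** Only the nurse, the physiotherapist and the Clinical Research Unit are shown handling the allocation. A reader might infer that the supervising cardiologist is told the arm. The article never says so; it speaks of staff in general and makes no exception.
- **No need to know is an argument from silence.** A condensed article does not list every duty. If the tests fall exactly at months 1 and 3, training could run to about day 103 (30 + 3 + 70), against about day 91 for visit 2. Some patients might then still be in training when tested, although Procedure places the sessions between the two visits. Masking may not be workable for every patient.
- **Masking the cardiologist leaves other sources.** The patient knows the arm, and it is the patient's own exhaustion that can end the test. The nurse at the test may know it too.
- **The size is hypothetical.** Treadmill time is not among the listed variables, so turning a bias in seconds into a false-positive rate has no basis in the document.
- **A partial check exists.** Real and theoretical maximum heart rate are both recorded, so effort can be compared between arms. Real maximum is itself exposed to the bias, so the check is weak.
- **Openness is already disclosed** as a limitation, and the primary outcome has a masked committee.

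The objection that this is only detail left out of an article does not stand. Limitations states positively that staff will know the arm, and masked assessment is stated for the primary outcome alone. That committee also shows that masked assessment was thought feasible in this open trial.

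**Conclusion.** The point holds as a modest, inexpensive improvement to one secondary outcome. The visit 2 test can end on symptoms, is run by staff whom the plan describes as aware of the arm, and has no stated masking. Nothing in the article requires the cardiologist to know the allocation at that visit, so the staff-driven part of the bias is partly avoidable.

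A reader might infer that a positive functional-capacity result could not be attributed to training at all. The documents do not support that. Some stopping reasons and variables are less exposed, effort can be partly checked, and nothing shows that the bias will occur. Nor would masking the cardiologist make the result free of bias.

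The figures of about 13% to 39%, against 2.5% nominal, rest on an assumed bias of 0.1 to 0.2 SD and on 139 tested per arm. They are illustrative only.

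**What to change.** In Procedure, add for the visit 2 test:

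- the test request is sent without the arm;
- the supervising cardiologist is not told the allocation, where feasible;
- patients are asked not to disclose it;
- the cardiologist and the nurse use the same standard encouragement for all patients.

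Amend Limitations to say that patients and the staff who deliver the intervention know the group, that the visit 2 cardiologist is kept unaware where feasible, and that functional capacity is still to be interpreted as a result from an open trial.

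The criteria for ending the test need no change. The cost is a procedural instruction and a request form without the arm, with no extra tests or staff. The limit is incomplete masking: some patients will disclose, and the patient's own effort and an aware nurse remain sources of bias.
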